## **B. Innovation**

Since the mid-1990s, studies conducted by different investigators from both the United States (25, 31, 35, 44-47) and Europe (34, 36-41, 48, 49) have shown that acupuncture can have a

positive effect on symptoms related to radiation-induced xerostomia. Patients have reported relief in as few as 5 treatments with benefits lasting up to 3 years. Only our two studies (see sections C.8 and C.9), however, have examined whether acupuncture can prevent this often-debilitating side-effect of radiation treatment from occurring or if it can diminish the symptoms once it develops. There have also been no large, definitive, phase III placebo- controlled trials to determine whether acupuncture is an effective treatment for managing radiation-induced xerostomia.

Most previous trials of acupuncture to treat xerostomia have been single-institution studies. Furthermore, few studies have examined NPC, as it is not prevalent in Western countries, which is where all the previous research on acupuncture for xerostomia has been conducted. The proposed trial is unique in that we will extend the findings from our phase II trial and pilot placebo-controlled trial conducted at Fudan Cancer Hospital by now conducting a multi-center, placebo-controlled, phase III clinical trial of acupuncture to prevent xerostomia in patients with NPC and other head and neck cancers (mainly oropharyngeal cancer). The inclusion of a placebo control group will allow us to more definitively determine the benefits of acupuncture for preventing this difficult-to-manage side effect of radiotherapy to the head and neck. Examining the effects within two different cancer populations, at two different centers, in two different countries, will increase the generalizability of our findings. Importantly, in addition to using validated self-report measures for xerostomia accepted by the Food and Drug Administration as the “gold standard” for the approval of treatments for xerostomia, we will assess more general aspects of QOL, assess objective measures of salivary flow, and quantify changes in potential mechanisms through assessment of salivary constituents.

Another innovative aspect of this study involves evaluation of participant expectations on outcomes. This will allow further exploration of how psychological phenomena may be related to outcomes in acupuncture research. Although well-conducted, placebo-controlled clinical trials have offered insights into the efficacy of acupuncture, the substantial effect seen in many placebo acupuncture groups presents a significant challenge in interpreting treatment results. Many studies, including several meta-analyses (50-56), have found that both real and placebo acupuncture produce statistically and clinically significant changes when compared to no treatment or standard/enhanced medical care. These findings suggest that the effect found in placebo acupuncture groups cannot be entirely attributed to either regression to the mean or natural disease processes; thus, the “non-specific” effect of acupuncture must be responsible in part for patients’ clinical response. Nevertheless, until we can parse the components that make up the “non-specific” effect, this effect, powerful as it may be, is likely to be discarded from a scientific standpoint. Years of psychological research has found that expectancy is one of the central pieces in this so-called “non-specific” effect. In particular, response expectancy, a form of outcome expectancy defined as “expectations held by the individual about one’s own emotional and physiological response” related to a situation or therapy, may produce important clinical changes (57). In a systematic review, Crow et al. (58) showed that when clinicians stated positive outcome expectations as opposed to uncertain expectations, most studies found improvements in patient self- reports of anxiety, pain, and distress.

A few studies have explored the association between expectancy and clinical outcomes in the context of acupuncture (59, 60). While these studies provided preliminary evidence that greater expectancy may produce better clinical response, none used a validated instrument to measure expectancy. In the proposed study, we will use an expectancy questionnaire that has been validated in both English and Mandarin (61). Investigating expectancy as part of the complex mind-body interactions of acupuncture care will likely yield important knowledge that

is both scientifically sound and clinically meaningful to patients who suffer from xerostomia and other distressing symptoms.

## **C. Approach**

### **C.1 Overview and Design**

The primary purpose of this trial is to investigate whether true acupuncture is more effective than sham acupuncture or standard care for preventing radiation-induced xerostomia. Prior to radiation therapy, patients will be randomized into three groups: G1 (n=100) will receive true acupuncture, G2 (n=100) will receive sham acupuncture, and G3 (n=100) will receive standard care. Patients in the acupuncture treatment groups will receive up to 21 treatments over the course of radiotherapy with no more than 3 treatments per week. The duration of acupuncture therapy in the proposed study is the same as in our pilot trials. It has been shown to have a good effect in our phase II trial and small placebo controlled trial conducted at Fudan Cancer Hospital. Furthermore, inconvenience is minimized for participants because acupuncture is provided on the same day as radiation therapy.

Potential study participants will be identified by faculty in the departments of Radiation Oncology at Fudan Cancer Hospital and M. D. Anderson and referred to the research nurse for assessment of eligibility and informed consent counseling. Potentially eligible patients will be contacted in person when they are in the clinic so that the research nurse can describe the study in detail, answer the patients' questions, and assess their interest in the study. Approximately half the patients will be recruited from each center (193 patients at MD Anderson and 242 at Fudan) for a total sample size of 435 patients (see Appendix D. Study Schema, Study Schedule, Study Timeline).

### **C.2 Eligibility and Participants**

**Inclusion criteria:** Adult  $\geq 18$  years of age and able to give informed consent; Diagnosed with head and neck cancer, which will be primarily oropharyngeal, and scheduled to undergo IMRT with or without concurrent chemotherapy at M. D. Anderson. Treatment plan that includes external beam radiation at a mean dose of at least 24 Gy or more to one of the parotid glands (the other gland can receive less than 24 Gy); Anatomically intact parotid and submandibular glands; Karnofsky performance status  $> 60$  (see Appendix E);

**Exclusion criteria:** History of xerostomia prior to head and neck radiation therapy or history of Sjögren's disease or another underlying systemic illness known to cause xerostomia; Prior head and neck radiation treatment; Suspected or confirmed physical closure of salivary gland ducts on either side; Known bleeding disorders or taking any dose of warfarin or heparin; Upper or lower extremity deformities that could interfere with accurate acupoint location or alter the energy pathway as defined by traditional acupuncture theory; Local skin infections at or near the acupuncture sites or active systemic infection; History of cerebrovascular accident or spinal cord injury since the mechanism of acupuncture may be associated with central nervous system activity; Mental incapacitation or significant emotional or psychiatric disorder that, in the opinion of the investigator, precludes study entry as these patients may not be able to cooperate with this slightly invasive procedure or with the data collection process; Current acknowledged use of any illicit drugs or evidence of alcohol abuse as defined by The American Psychiatric Association criteria (62); Current acknowledged use of other alternative medicines, such as herbal preparations, that could affect salivary function. If a patient is using any salivary substitute, they will be asked to refrain from using for at least 24 hours prior to saliva and questionnaire data collection. Each patient will be asked for a list of herbal supplements they are currently taking, and this will be reviewed on an individual basis.

Patients will be excluded if they are taking any herbs known or suspected to affect salivary function. Participants taking amifostine, cholinergic agonist medications (pilocarpine, cevimeline), certain beta adrenergic antagonists, anticholinergic agents, saliva substitutes or other medications known to affect salivary function will also be excluded (see Appendix F). If a patient reports use of one of the prohibited medications, they will be considered non-compliant and dropped from the study. Finally, participants will be excluded who are currently receiving acupuncture for any condition or if they have ever used acupuncture before. If a participant is admitted to the hospital for any reason during the treatment period, an in-patient order for treatment will be requested.

**Participants:** Over 400 patients undergo IMRT radiation for head and neck cancer each year at M. D. Anderson or one of its satellite clinics. Within the next 2 years at least two more satellite clinics will open, increasing the possible patient base. At Fudan Cancer Hospital, approximately 450 patients undergo IMRT for NPC each year. Our pilot study experience at both institutions suggests that approximately 70% of these patients will be eligible for the proposed study. Therefore, at least 500 patients will be eligible per year for a total of over 1500 patients during the 36 months designated for recruitment.

All eligible patients will be asked to participate. We expect a relatively modest acceptance rate of approximately 60%. Patients generally decline either because they do not want to be randomized or because of time constraints. This conservatively estimated patient accrual rate would permit us to recruit at least 70 patients per year at each institution. In our previous studies, the attrition rate was less than 20%; however with longer follow-up, we expect the rate will increase somewhat. Thus, with even slightly higher attrition, we will still be able to accrue at least 50 evaluable patients per year per institution, for a total of 300 evaluable patients over the approximate 3 years of recruitment (n=100 per group; n=125 per group before attrition).

### **C.3 Procedures**

After informed consent and prior to randomization and radiation treatment, the research nurses will collect baseline measures. Patients will be informed the study is examining the effects of two different forms of acupuncture delivered during radiotherapy. This is important because in most previous sham-controlled acupuncture trials patients could accurately guess group assignment. In this trial, patients in both acupuncture groups are in fact getting real needles inserted at real acupuncture points on the body and, therefore, this is technically classified as real acupuncture. Therefore, this is not deception and, in fact, we do not actually know whether G1 will have any better outcomes than G2. In reality, we are testing two forms of acupuncture. When a patient in G2 finishes the trial, we will debrief them to let them know that they were in an acupuncture group that we were uncertain if it would work or not. We will offer them three free sessions of acupuncture after the 12 month follow-up assessment.

A modified medical examination of participants will be obtained that includes a medical history and physical; review of systems, concomitant medications, and head and neck malignancy; surgical and radiation history; and planned radiation treatment. Self-report measures and sialometry measurements, including unstimulated whole salivary flow rate (USFR) and stimulated whole salivary flow rate (SSFR), will be completed. In order to identify potential mechanisms associated with acupuncture elicited stimulation of saliva secretion, measurement of pH and buffering capacity will be performed on fresh saliva from SSFR. Samples will then be frozen for later analysis of viscosity, total protein and neuropeptides, including CGRP, and VIP. After all analyses are complete, the saliva samples will be

destroyed.

At each acupuncture visit, vital signs (blood pressure, pulse) will be taken, and medications will be reviewed prior to the acupuncture treatment. Since the SC group does not receive acupuncture, they will not have vital signs taken and medications will not be reviewed on a weekly basis. All measures will be collected again during the course of radiation treatment (mid-treatment; except the assessment of salivary constituents), at the end of the radiation treatment period, and at 2-4, 5-9, and 10-15 months. These assessments may be collected over the phone if the patient is unable to come to MD Anderson. Patients will also be asked to complete a form about their oral hygiene. All patients will be provided with standard oral care recommendations. These include keeping their mouth clean by brushing their teeth at least two times a day and preferably after each meal. They will be also encouraged to not use candies, lozenges, or drink sugary beverages. They will also be told to consume up to 1.5 liters a day of water to help diminish the effects of radiation-induced xerostomia and keep hydrated.

Follow-up assessments will be obtained 2-4, 5-9, and 10-15 months after the end of radiation treatment for a total of 6 assessments (baseline; middle of radiotherapy; end of radiotherapy; and 2-4, 5-9, and 10-15 months after the end of radiation treatment). Participants will be given a small gift certificate (100 RMB [approximately \$15] value at Fudan Cancer Hospital; \$35 value at M. D. Anderson) for completing each assessment. After all data are collected at the 12-month follow-up visit, patients in the G2 and G3 study arms will be offered true acupuncture treatment for free for one week (3 treatments). For the complete study schema, schedule, and timeline please see Appendix D. All data collection will be conducted by research staff who are blinded to group assignments. A procedures manual will be developed that will include all aspects of conducting the trial, including the acupuncture treatments.

Patients will be randomized by a form of adaptive randomization, called minimization, because simple randomization could result in covariate imbalances (63). Statistical adjustment of covariates can take imbalances into consideration, but results are generally more credible when they are obtained from groups with comparable baseline distributions. In minimization, group assignment is done sequentially. In this study, the patient characteristics used for group assignment will be stage of disease, age (running mean), sex, the mean planned parotid doses (left and right side will be calculated separately and balanced between groups; <10, 10-<20, 20-<26, 26-<30, 30-<35, 35-<40, 40-<50, 50-<60, ≥60), induction therapy (yes/no), and concurrent chemotherapy (yes/no). Randomization will be conducted at each site separately. This will ensure equal distribution of all factors across all groups and balanced at each site. Information on group assignment will be only communicated to the acupuncturists by the data managers to insure that the research staff remains blinded.

Treatment will be withheld if lab values are not within an acceptable range (ANC>500; platelet count>20K/ml; INR, 3.0); if the study participant is diagnosed with a mental incapacitation or significant emotional or psychiatric disorder that interferes with his/her ability to cooperate with study procedures; or if a participant receives any heparin or warfarin during the treatment period.

Participants will be dropped from the study, at any point during the study, if the participant begins taking a prohibited medication (Appendix F) or if the participant encounters a cerebrovascular accident or spinal cord injury.

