### **C.5 Evaluation**

All questionnaires will be administered at the patient's clinic visits. If, however, there are time constraints, patients will be given a self-addressed stamped envelope in which to return the questionnaires. Baseline assessments will be completed within 7 days prior to starting radiotherapy, and patients will then complete the same assessments again at middle and end of radiotherapy and 2-4, 5-9, and 10-15 months after the end of radiotherapy. At middle and end of radiotherapy, data will be collected before acupuncture treatment. For patients at

Fudan Cancer Hospital, the questionnaires were forward and backward translated into Mandarin Chinese (the MDASI and FACT-G were also validated in Mandarin Chinese; see Appendix H). All of the questionnaires and saliva collection techniques have been used successfully at both institutions.

To determine if true acupuncture is more effective than sham acupuncture or standard care for reducing the incidence of radiation-induced xerostomia we will evaluate xerostomia graded according to Common Terminology Criteria for Adverse Events (CTCAE) (78) (see Appendix I).

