#### **d. Expectations**

Acupuncture Expectancy Scale (AES): To determine the relationship between outcome expectancy related to acupuncture and clinical response, we will use the Acupuncture Expectancy Scale. This 4-item instrument was developed by Mao et al. and found to be reliable (Cronbach's  $\alpha$  of 0.82) and valid by positive correlation with patient self-reported efficacy and satisfaction (61). The scale was further validated among cancer patients who were mostly acupuncture naïve (57). Expectancy of a benefit from acupuncture appeared to be increased by educating patients on the scientific theory and clinical evidence of acupuncture. Higher expectancy was also found in patients who had previously participated in an acupuncture trial compared with those who had not participated in an acupuncture trial (57). The scale has been translated and validated in Mandarin in China. In the proposed study, we will evaluate expectancy as a predictor of response to acupuncture. This questionnaire will be completed at baseline by all participants. Patients in the acupuncture treatment groups will complete the form again during the middle and at the end of radiotherapy.

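### Repeating the expectancy form only in the acupuncture arms lets staff who collect all data recognise standard care, so the blanket blinding claim is supported only for true versus sham

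*Supplement*

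**What the plan says.** All references are to the Final Protocol.

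- **Blinding claim (C.3 Procedures).** "All data collection will be conducted by research staff who are blinded to group assignments". It is not limited to any pair of arms.
- **Mechanism (C.3 Procedures).** "Information on group assignment will be only communicated to the acupuncturists by the data managers to insure that the research staff remains blinded". No other safeguard is described.
- **Expectancy form (C.5 d, Expectations).** At baseline, "This questionnaire will be completed at baseline by all participants". Afterwards, "Patients in the acupuncture treatment groups will complete the form again during the middle and at the end of radiotherapy".
- **Who collects (C.3 Procedures).** After consent and "prior to randomization and radiation treatment, the research nurses will collect baseline measures". Later, "All measures will be collected again during the course of radiation treatment", and again at the end of radiotherapy and at three follow-ups. No separate assessor is named for CTCAE grading or saliva collection.
- **Timing (C.5 Evaluation).** "At middle and end of radiotherapy, data will be collected before acupuncture treatment". No interval is given.
- **Another procedure that differs by arm (C.3 Procedures).** "Since the SC group does not receive acupuncture, they will not have vital signs taken and medications will not be reviewed on a weekly basis".

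**The concern.** The blinding sentence and the AES schedule do not fit together. Collecting the AES is part of collecting data. Someone who collects it from true and sham patients but not from standard-care patients knows which patients are in standard care, and that is part of what the sentence says they do not know.

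Standard care is a named comparator in the primary aim and in secondary aims 2 and 3. The end of radiotherapy, one of the two visits with the arm-specific form, is the time point used to justify the sample size and the one at which all three arms are compared (C.6 a). Standard-care patients know they receive no acupuncture, so the self-reported XQ is open in that comparison. A reader who trusts the blinding sentence would treat the staff-dependent measures, above all the CTCAE grade behind secondary aim 2, as a blinded check on the open XQ comparison. The plan as written does not secure that.

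**Working it through.** The plan states no figure to reproduce. The check sets the passages side by side and then counts what is affected.

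**Consistency**

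1. C.3 puts all data collection in the hands of research staff blinded to group. The AES is one of the measures, so it falls under that sentence.
2. At baseline the AES says nothing about arm: everyone completes it, and baseline measures are taken before randomization.
3. At the middle and end of radiotherapy, C.5 d asks for it in the two acupuncture arms only. Whoever gives it or takes it back learns from its presence or absence whether the patient is in an acupuncture arm or in standard care.
4. The form is the same in the true and sham arms, so it carries no information about true versus sham.
5. The mechanism in C.3 restricts allocation to the acupuncturists. To omit the form correctly for standard-care patients, the collector needs part of the information being withheld. Within the text shown, both rules can be followed only if someone other than the outcome collectors handles the repeat AES, and no such person is named.
6. The blinding argument in C.4 b (Sham acupuncture) concerns true versus sham. The pilot cited there had two acupuncture arms and no standard-care arm, so it cannot show that staff stay blind to standard care.

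**What is affected**

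- Assessments: five follow baseline (middle of radiotherapy, end of radiotherapy, 2-4, 5-9 and 10-15 months). The AES differs by arm at 2 of 5.
- Comparisons: three pairs of arms. True versus standard care and sham versus standard care are affected, so 2 of 3.
- Patients, assuming equal arms of the planned 435: 435 / 3 = 145 per arm. The repeat AES is due in 2 × 145 = 290 and not due in 145. These are enrolment figures. C.6 c allows up to 31% drop-out and plans on 300 evaluable, 100 per arm; at that level the counts would be 200 and 100.

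**Exposure by outcome, against standard care**

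- XQ completed by the patient: open whatever staff know.
- XQ by telephone (C.5 a, item i): a staff member is involved, but this route applies only when the patient cannot come to MD Anderson.
- CTCAE xerostomia grade (C.5 Evaluation; C.6 a): a grading whose grader is not named. This is the main exposure.
- Saliva flow (C.5 b): collected under a fixed, timed script and weighed, so there is less room for staff influence.

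The documents give no figure from which a bias in any of these could be calculated.

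**The case against.** The strongest reply is that the protocol never says who hands out the AES, who grades CTCAE or who collects saliva after baseline. The AES is a four-item self-report form, and C.5 Evaluation lets patients return questionnaires in a stamped envelope when time is short. C.3 leaves the detail of conduct to a procedures manual that is not shown. This stands to the extent that shared staffing is a reading of the blanket sentence and of the absence of any separate assessor, not a documented fact. It does not rescue the sentence, which covers all data collection and names no exception.

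Three stronger readings are tempting, and the documents support none of them.

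- A reader might infer that collectors see acupuncture patients immediately before a session and so recognise them. C.5 says only that collection comes before treatment. C.1 puts acupuncture on the same day as radiotherapy, so one common slot for all three arms would satisfy the rule without revealing arm.
- A reader might take the vital-sign and medication-review difference as a second disclosure. It describes acupuncture visits, and nothing says outcome staff carry out those checks.
- A reader might infer complete unblinding to standard care throughout, leaving no independent check on XQ. The arm-specific form occurs at two of five assessments; beyond those, knowledge persists only if the same staff continue. Weighed, scripted saliva collection also keeps much of its value.

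It is also fair to say that the primary outcome is little changed, since XQ against standard care is open in any case.

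**Conclusion.** The concern holds in a limited form. As written, the claim that all data collection is blind to group cannot be met against standard care at the middle and end of radiotherapy, because staff who collect all data would see a form completed only in the acupuncture arms. It touches two of the three pairwise comparisons and leaves true versus sham intact. The outcome most exposed is the CTCAE xerostomia grade, then any telephone XQ, then saliva flow to a lesser degree. No size or direction of bias can be derived.

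This rests on two assumptions: that the sentence means what it says, so the repeat AES is within the blinded staff's work, and that the unseen manual does not assign it elsewhere. Carry-over to the three follow-ups rests on a third, that the same staff continue. The correction is worth making because the claim is broader than the procedures support and the remedy is cheap.

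**What to change.** 1. Keep the repeat AES away from the outcome collectors. Have it self-completed and returned sealed to the data manager, who already holds allocation. The acupuncturists should not administer it: they know true from sham, and an expectancy form given by them could bias the one comparison that is now protected.
2. Use the same assessment-slot procedure in all three arms at the middle and end of radiotherapy, without telling the collector whether a session follows.
3. Restrict the C.3 statement to staff being blinded to true versus sham. Report the CTCAE and salivary flow comparisons with standard care as not assured to be assessor-blind. The narrower wording is needed even with steps 1 and 2, since standard-care patients know their own arm.

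The cost is procedure wording and slight extra handling of one four-item form. No visits, patients or outcome measures change.

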### **C.8 Adverse Events**

Acupuncture is a safe technique with few complications. The majority of reported adverse effects are best attributed to insufficient basic medical knowledge, inadequate acupuncture education, or lack of compliance with standardized practice of clean needle technique (104). Several studies by different investigators have shown that most serious adverse events are due to a lack of education or negligence on the part of the practitioner and are not due to the treatment itself (105-109). The side effects most commonly reported when acupuncture is performed correctly by properly trained personnel are relatively minor and include fainting, nausea, vomiting, bruising, and mild discomfort (105-109). In the past, patients occasionally developed contact dermatitis to components in the needles (110, 111), but this currently is rare with improved manufacturing techniques for the stainless steel needles.

For higher risk patients (i.e., those with heart disease or neutropenia), special precautions may be necessary such as avoiding the use of electrostimulation in patients with pacemakers or taking additional measures to prevent infection in patients with compromised immunity (112). Electrical stimulation will not be used in this study, and patients with evidence of infection or compromised immunity will not be included. Although the likelihood of acupuncture-induced infection in this study is low, procedures will be treated as invasive medical procedures and performed using aseptic techniques. The acupuncture needles used will be sterile and individually packaged. Reportable adverse events will include:

- a. syncope
- b. infection at the acupuncture site
- c. allergic contact dermatitis at the acupuncture site
- d. excess bleeding at the acupuncture site

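### The C.3 lab limits for withholding acupuncture need repair: the platelet unit is literally 1,000-fold too low, INR has no direction and ANC has no unit

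*Supplement*

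**What the plan says.** In the Final Protocol, C.3 (Procedures) sets the rule for holding a session: "Treatment will be withheld if lab values are not within an acceptable range (ANC>500; platelet count>20K/ml; INR, 3.0". The same sentence also withholds treatment for a disabling psychiatric disorder and for any heparin or warfarin given during the treatment period. The Summary of Protocol Revisions (entry approved 4/30/2012) records that the rule was added to clarify what happens when, among other things, blood counts change during treatment.

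The checks that C.3 names at each session are these: "At each acupuncture visit, vital signs (blood pressure, pulse) will be taken, and medications will be reviewed prior to the acupuncture treatment".

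On entry, C.8 (Adverse Events) states that "patients with evidence of infection or compromised immunity will not be included" and adds that "procedures will be treated as invasive medical procedures and performed using aseptic techniques". The nearest exclusion in C.2 (Eligibility and Participants) is "Local skin infections at or near the acupuncture sites or active systemic infection". C.2 admits patients "scheduled to undergo IMRT with or without concurrent chemotherapy", and the minimization factors in C.3 include "induction therapy (yes/no), and concurrent chemotherapy (yes/no".

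**The concern.** A withholding rule works only if the person about to place the needles can compare a lab report with the limit and get one answer. Here the platelet limit carries a unit that makes it far too low if taken literally, the INR limit does not say which side of 3.0 is acceptable, and the ANC limit has no unit. Two centers in two countries apply the rule, so the printed text should be enough by itself.

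Both acupuncture arms are exposed, because both include penetrating needles. From C.4, true acupuncture uses 13 (Ren 24; LU 7 and K6 on both sides; 8 ear points) and sham uses 9 (Gb 32; 8 ear points). C.1 allows up to 21 sessions. C.2 also provides that "If a participant is admitted to the hospital for any reason during the treatment period, an in-patient order for treatment will be requested". That request does not bypass C.3, but it does mean the limits may be read outside the usual clinic.

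The entry wording is a smaller matter. C.8 gives an exclusion that C.2 does not list and that neither section defines, in a population where prior induction therapy is expected often enough to be a balancing factor.

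**Working it through.** **Platelets.** The input is 20K per ml (C.3).
- As printed: 20,000 per mL ÷ 1,000 microlitres per mL = 20 per microlitre = 0.02 × 10^9/L.
- If per microlitre was meant (assumption): 20,000 per microlitre = 20,000,000 per mL = 20 × 10^9/L.
- Ratio: 20,000,000 ÷ 20,000 = 1,000.

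Taken literally, the limit would in effect never withhold a session.

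**ANC.** The input is 500 with no unit (C.3).
- Per microlitre (assumption): 500 per microlitre = 0.5 × 10^9/L.
- Per mL, carrying over the unit printed for platelets: 500 ÷ 1,000 = 0.5 per microlitre.

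Only the first is a workable limit.

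**INR.** The input is a comma followed by 3.0 (C.3). Read in parallel with the two greater-than limits beside it, values above 3.0 would be acceptable. Read as a bleeding safeguard, values below 3.0 would be. The second is the plausible intent (assumption), but the text does not say so.

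**Could this be a PDF reading error?** The log entry of 4/30/2012 carries the rule separately. It also prints INR with a comma and no sign, and it also has ml. The greater-than signs survive in both places, and less-than signs survive in the parotid dose bands in C.3. A lost INR sign is therefore unlikely to come from the reading. For ml the log is weaker evidence, since both texts may descend from one source and a micro sign turned into m is possible. If so, the platelet limit is correct and only the ANC unit and INR direction need repair.

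**Scope.** 435 ÷ 3 = 145 per arm; 2 needled arms × 145 = 290 patients. This assumes equal allocation, as in the equal group sizes in C.1. The documents do not say how many patients reach low counts, so no number of affected sessions can be given.

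**Entry wording, side by side.**
- Infection: excluded in C.8 and carried out in C.2.
- Compromised immunity: excluded in C.8, with no criterion in C.2 and no definition in either section.
- Chemotherapy: concurrent treatment is allowed in C.2, and induction and concurrent treatment are both minimization factors in C.3.

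An exclusion may stand outside C.2. C.4 has one for the Ren 24 site, but it names what to look for (skin irritation or infection), and the C.8 clause does not.

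**The case against.** The strongest reply is that this is proofreading. ANC above 500 is workable only per microlitre, INR can only be an upper bound in a bleeding safeguard, and no clinician would apply 20 platelets per microlitre. INR is also largely backed up: the same sentence withholds treatment for any heparin or warfarin, and C.2 excludes users of either and patients with known bleeding disorders. The procedures manual, which is not shown, may print the limits properly. Much of this stands, and it keeps the point minor. It does not remove the point, because a manual does not correct the protocol text and the correction is a few characters.

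On entry, the reply is that the exclusion does exist, in C.8, and that C.2 leaves other terms to clinical judgement. Concurrent chemotherapy accompanies radiotherapy, while randomization precedes it, so being scheduled for it does not make a patient immunocompromised at entry. That also stands. What remains is an undefined term that C.2 does not carry and that fits awkwardly with patients already given induction therapy.

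A reader might go further in three ways that the documents do not support:
- That C.8 and C.3 contradict each other. C.8 can be read as governing entry, and the log shows that C.3 was written for the treatment period.
- That no lab values are collected. C.3 names only vital signs and medications at visits, but Appendix D and the manual are not shown.
- That patients would be harmed. The documents give no rate of low counts. They do provide infection exclusions, aseptic technique and reporting of site infections.

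**Conclusion.** The C.3 withholding rule is the only count-based needling safeguard shown, and its limits need correction. The platelet limit is 1,000-fold too low as printed, on the assumptions that per microlitre was intended and that ml is truly in the source file. The INR direction and ANC unit are missing whichever way ml is resolved. The rule covers about 290 of 435 planned patients under equal allocation. The 1,000-fold figure measures the misprint and is no estimate of sessions wrongly given.

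The mismatch between C.8 and C.2 on compromised immunity is real but secondary. Severity is minor. Neither part touches the primary analysis, the sample size or the type I error.

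**What to change.** In C.3 print: ANC >500 per microlitre (0.5 × 10^9/L); platelets >20,000 per microlitre (20 × 10^9/L); INR <3.0. The sponsor should confirm that these are the intended limits before the text is changed.

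Separately, align C.8 with C.2. Either add to C.2 the entry criterion that compromised immunity was meant to express, or reword C.8 to say which patients may enter and that the C.3 limits apply to them during treatment. The choice is the sponsor's.

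Neither change requires a rule on which lab value to use, and I would not add one that lets sessions go ahead on values from before radiotherapy, since that could weaken the safeguard.

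The cost is a short amendment to C.3 and to C.2 or C.8. The C.3 correction needs no new blood draws, and no analysis changes.
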